### Design

This study will be a single-center, equally randomized, two-armed, parallel, stratified (gender), subject-assessor-blinded, sham-controlled pilot trial. This trial is being conducted at the Pain and Spine Center, Dunsan Korean Medicine Hospital of Daejeon University (DKMHDU), Korea.

A total of 50 participants diagnosed with CNP will be recruited from the Clinical Trial Center of DKMHDU in Daejeon through advertisements in local newspapers, on hospital websites and bulletin boards, in information leaflets, etc. The recruitment period will run from May 2017 to December 2017. Clinical research coordinators will interview all potential participants over the telephone and schedule screening visits. At the screening visits, all potential participants will be informed of the objectives and the overall procedure of the trial and will be asked to provide written informed consent. Study volunteers will go through a screening process, which will include radiography of the cervical spine and physical examinations, to verify the diagnosis of non-specific CNP.

At visit 1, an eligible participant will receive baseline assessments, including the use of the acupuncture expectancy scale [30, 31], and will then be randomly allocated into one of two groups: the real TEA group and the sham TEA group. The real TEA group will receive TEA treatment at local acupoints in the neck region. The sham TEA group will receive the same treatment as the real TEA group, but with a sham device with the thread removed. Both groups will receive treatment once a week for a total of four sessions. The real TEA and the sham TEA will be described to the participants as “classical TEA” and “non-classical TEA,” respectively. Researchers will explain to the participants that the term “classical TEA” is “typically used in Korean Medicine clinics” while the term “non-classical TEA” is “rarely used in Korean Medicine clinics” [32, 33]. Outcome measures will be assessed before the treatment (week 1), 2 weeks after the first treatment (week 4), and 2 weeks (week 6) and 4 weeks (week 8) after the last treatment. A flowchart of the study is illustrated in Fig. 1, and the clinical trial schedule is presented in Fig. 2.

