### Pain

The secondary outcome for pain will be the mean change on the 100-mm VAS for CNP from the baseline to week 3, week 6, and week 8, respectively.

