### Global assessment

The participants’ global assessment will be performed using the Patient Global Impression of Change (PGIC), a self-reported 7-point categorical scale that is used to evaluate the overall improvement after treatment [57]. Participants will evaluate themselves as to the improvement of their symptoms at week 6 and week 8 from baseline by selecting one of the following seven options: (1) very much improved, (2) much improved, (3) minimally improved, (4) no change, (5) minimally worse, (6) much worse, or (7) very much worse.

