### Statistical methods

#### Sample size

This pilot RCT is designed as a preliminary to a full-scale confirmatory trial. Therefore, we assume that a total of 50 participants will be an acceptable sample size, considering 20 participants in each group with a 20% drop-out rate.

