#### Statistical analysis

Data will be analyzed by an independent statistician who is blinded to the group allocation and who will use the Statistical Package for the Social Sciences (SPSS) Version 23.0 (IBM Inc., New York, NY, USA). The analysis set will consist of the Intent-to-treat (ITT) set, Per-protocol (PP) set, and Full Analysis Set (FAS). The ITT set will include all participants as originally allocated after randomization. The PP set will include the participants who completed three or more treatment sessions (75%) and the entire trial without any major violation of the protocol. Participants who are assessed at least once after random allocation will compose the FAS, which will be used for the main analysis of the treatment outcomes. Safety will be analyzed using the ITT set. The significance level will be set at *p* < 0.05. Missing data will be handled using the last-observation-carried-forward (LOCF) method.

The demographic and baseline characteristics, such as age, gender, medical history, duration of CNP and treatment expectancy, will be summarized for each treatment group. Depending on whether a normal distribution is found or not, baseline assessments for homogeneity will be conducted using the Wilcoxon rank sum test or the *t* test for continuous variables and Fisher’s exact test or the chi-square test for categorical variables.

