The primary outcome, the mean changes from baseline to week 6 in the VAS scores, will be compared between the two groups by using the *t* test or analysis of covariance (ANCOVA). If the baseline difference in the VAS score between the two groups is statistically significant, an ANCOVA will be performed with the baseline VAS score as a covariate and the study group as a fixed factor. The paired *t* test or the Wilcoxon signed rank test will be conducted to compare the treatment outcomes before and after intervention in each group. In addition, a repeated-measures analysis of variance (ANOVA) will be used to further confirm the differences in the trends of the visit. The secondary efficacy outcomes will be evaluated using the Wilcoxon rank sum test or the *t* test for continuous variables and Fisher’s exact test or the chi-square test for categorical variables. For safety assessments, all adverse events will be recorded as frequencies with percentages and durations. The chi-square test or Fisher’s exact test will be used to evaluate the statistical significance of between-group differences in the frequencies of adverse events. The duration of each adverse event will be compared between the two groups by using the Wilcoxon rank sum test or the *t* test. Subgroup analyses based on baseline characteristics will also be performed for the primary and the secondary outcomes.

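### Continuous secondary outcomes are compared with no baseline covariate, and the ordered PGIC falls under tests that ignore order: a minor, avoidable loss of precision

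*Protocol article*

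**What the plan says.** All references are to the protocol article.

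- **Tests for secondary outcomes (Statistical analysis).** "The secondary efficacy outcomes will be evaluated using the Wilcoxon rank sum test" or the t test when the variable is continuous, and Fisher's "exact test or the chi-square test for categorical variables". No covariate is named and no ordinal or trend test is listed.
- **ANCOVA (same section).** It is described only for the primary VAS change, and only if the two groups differ significantly on baseline VAS.
- **Other analyses (same section).** Within-group paired tests are planned, and a repeated-measures ANOVA across visits whose outcomes are not listed.
- **PGIC (Global assessment).** It is "a self-reported 7-point categorical scale that is used to evaluate the overall improvement after treatment". Its seven options run in order from very much improved to very much worse, and it is rated at weeks 6 and 8.
- **Secondary VAS (Pain).** It is the "mean change on the 100-mm VAS for CNP from the baseline to week 3, week 6, and week 8, respectively".
- **Baseline data (Design; Outcome measurement).** Outcomes are assessed before treatment. Gender is the stratification factor.
- **Size (Sample size).** "a total of 50 participants will be an acceptable sample size", "considering 20 participants in each group with a 20% drop-out rate".

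**The concern.** NDI, PPT, HADS and EQ-5D are measured before treatment, yet the named test for each uses no baseline covariate under any condition. In a small trial the baseline score is usually the strongest predictor of the follow-up score. Leaving it out widens the confidence interval and lets a chance baseline difference carry into the estimate.

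The PGIC raises a separate matter. Its information lies in the order of the seven options. Chi-square and Fisher's exact test on a 2 × 7 table give the same p-value however the columns are rearranged, so they spread their power over patterns of no interest as well as over a general shift towards improvement.

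At stake is the precision of the secondary estimates. The validity of the trial and the primary result are not affected.

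**Working it through.** **1. The plan's own figure.** 20 evaluable per arm with 20% drop-out: 20 / (1 − 0.20) = 25 per arm, and 2 × 25 = 50. This matches. The article gives no power, SD, effect size or baseline-to-follow-up correlation, so no power figure can be reproduced.

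**2. Inputs.** From the article: 20 to 25 per arm, equal allocation, and "The significance level will be set at *p* < 0.05" (sidedness not stated; two-sided taken). Assumed: correlation r between baseline and follow-up, equal SDs at both times, an effect of 0.5 follow-up SD, and the PGIC distribution in step 5.

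**3. Continuous outcomes.** In units of the follow-up variance, and ignoring the degree of freedom spent on each covariate, the variance of the comparison is proportional to:

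- raw follow-up score: 1
- change score: 2(1 − r)
- ANCOVA: 1 − r²

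So ANCOVA relative to change is (1 − r²) / [2(1 − r)] = (1 + r)/2, and ANCOVA relative to raw follow-up is 1 − r².

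| r | ANCOVA / change | ANCOVA / raw | Power at 20 per arm: raw, change, ANCOVA |
|---|---|---|---|
| 0.3 | 0.65 | 0.91 | 35%, 27%, 38% |
| 0.5 | 0.75 | 0.75 | 35%, 35%, 45% |
| 0.7 | 0.85 | 0.51 | 35%, 53%, 60% |
| 0.8 | 0.90 | 0.36 | 35%, 71%, 75% |

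(Power by normal approximation.) Against change scores at r = 0.5, 20 per arm would act like 20 / 0.75 = 26.7; at r = 0.7, like 20 / 0.85 = 23.5.

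**4. Chance imbalance.** With 20 per arm the baseline difference has standard error √(2/20) = 0.32 SD. If a difference of that size occurs and r = 0.5, a raw comparison is displaced by 0.5 × 0.32 = 0.16 SD and a change-score comparison by (0.5 − 1) × 0.32 = −0.16 SD. ANCOVA removes both. Averaged over randomizations the displacement is zero, so this is another view of the precision loss in step 3.

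**5. PGIC.** Assumed sham distribution, best to worst: 4, 16, 35, 33, 8, 3, 1%. A proportional-odds shift is applied to the real-treatment arm. At an odds ratio of 3, much improved or better goes from 20% (odds 0.25) to 0.75 / 1.75 = 43%. There were 3,000 simulated trials per setting, with Fisher's test in its 2 × 7 extension.

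| Per arm | Odds ratio | Chi-square | Fisher | Wilcoxon |
|---|---|---|---|---|
| 20 | 1 (no effect) | 2.3% | 4.2% | 4.3% |
| 20 | 2 | 8% | 11% | 21% |
| 20 | 3 | 20% | 26% | 47% |
| 20 | 4 | 32% | 39% | 64% |
| 25 | 3 | 27% | 32% | 54% |

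At 20 per arm and odds ratios 2 to 4, Fisher has 54 to 61% of the Wilcoxon power and chi-square 38 to 50%. Part of the chi-square deficit is conservatism, as its 2.3% rejection rate under no effect shows.

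**6. Sparse cells, without an assumed distribution.** With equal arms, an expected count of 5 in both arms needs a column total of 10. With 40 people and all seven options used, four such columns would leave nobody for the other three, so at most three columns qualify and at least 8 of 14 cells fall below 5. With 50 people at most four qualify, leaving at least 6 of 14 below.

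**The case against.** The strongest reply is that these are exploratory outcomes in a pilot with no power target, that unadjusted comparisons are valid under randomization, and that matching tests to individual outcomes often waits for an analysis plan. The first two points stand and set the severity. The third stands only in part: the article does name the tests, and under its wording the result is unadjusted comparisons and, for the PGIC, an order-ignoring test. That routing is inferred from two sections, since the Statistical analysis section does not mention the PGIC, and the Wilcoxon test is already on its list.

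Four stronger readings are tempting, and the documents do not support them.

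- **That no secondary outcome takes account of baseline.** Secondary VAS is a change score, the responder ratios are defined relative to baseline, and the PGIC is itself a rating of change with no baseline score.
- **That the variance is inflated by half or more.** The ratio of 0.51 needs raw follow-up scores and r = 0.7. For NDI, PPT, HADS and EQ-5D the article does not say whether raw or change scores are compared. Against change scores the saving is 10 to 25% for r from 0.8 down to 0.5.
- **That the choice of test is why a real PGIC shift would be missed.** At an odds ratio of 3 and 20 per arm, Wilcoxon also misses it 53% of the time. The main cause is the sample size, which the Discussion acknowledges.
- **That information for the main trial is lost.** SDs, correlations and category counts remain available whichever test is used, and the Objective does not single out secondary outcomes.

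**Conclusion.** The point holds as a minor one about efficiency. No baseline covariate is specified for the continuous secondary outcomes, and on the article's wording the ordered PGIC goes to chi-square or Fisher.

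The loss on continuous outcomes is moderate if change scores are used and larger if raw scores are used with a high correlation. It rests on assumed r. The PGIC loss is larger in relative terms: roughly 40 to 60% of the rank test's power at 20 per arm. It rests on an assumed sham distribution and a proportional-odds shift. The direction in both cases does not depend on the exact values: apart from the degrees of freedom it spends, ANCOVA is at least as precise as either alternative at every r shown, and a rank test is better aimed at a general shift in an ordered scale. The planned tests remain valid.

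**What to change.** In the Statistical analysis section, replace the sentence on secondary outcomes with wording to this effect:

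- NDI, PPT, HADS and secondary VAS (and EQ-5D, if it is scored as a continuous index, which the Quality of life section does not say) are compared by ANCOVA with that outcome's own baseline value and gender as covariates. The adjusted difference and its 95% confidence interval are reported. ANCOVA is used in all cases, without a prior test of baseline difference, so the conditional rule written for the primary outcome should not be copied here.
- PGIC at weeks 6 and 8 is compared by the Wilcoxon rank sum test already listed, or by a proportional-odds model, with counts per category shown. Chi-square and Fisher's test on the seven categories are dropped.
- Fisher's exact or chi-square stays for the binary responder outcomes.

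The cost is wording and one or two residual degrees of freedom per model. No new data, visits or participants are needed. The change should be made and dated before unblinded data are seen.

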## Abstract

**Background:**

This study aims to evaluate the efficacy and safety of thread-embedding acupuncture (TEA) with polydioxanone thread embedded at various acupoints, compared with sham TEA, for the treatment of non-specific chronic neck pain.

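### Adverse-event frequency is compared between arms only by a p<0.05 test with about 25 patients per arm; a risk difference with its interval should carry the safety comparison

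*Protocol article*

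**What the plan says.** The Abstract (Background) sets the aim: "This study aims to evaluate the efficacy and safety of thread-embedding acupuncture (TEA) with polydioxanone thread embedded at various acupoints, compared with sham TEA". The Design section describes the trial as "single-center, equally randomized, two-armed, parallel, stratified (gender"), and Sample size gives the numbers: "we assume that a total of 50 participants will be an acceptable sample size, considering 20 participants in each group with a 20% drop-out rate". No adverse-event rate enters that reasoning.

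Statistical analysis fixes the population and the threshold: "Safety will be analyzed using the ITT set. The significance level will be set at *p* < 0.05". It plans to describe adverse events by frequency, percentage and duration. For the comparison of frequencies it then commits to one method: "The chi-square test or Fisher’s exact test will be used to evaluate the statistical significance of between-group differences in the frequencies of adverse events". A second safety comparison follows directly: "The duration of each adverse event will be compared between the two groups by using the Wilcoxon rank sum test or the *t* test". Adverse events and safety also names duration as something to compare between groups. It adds causality and severity grading, reporting of serious events, and blood tests at screening and week 6.

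The article gives no expected adverse-event rate, no margin for harm and no rule for drawing a safety conclusion.

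**The concern.** The two arms receive the same needling and differ by the thread, so an excess of local reactions caused by the thread is a foreseeable question. The article itself lists pain, stiffness and irritation as treatment-related events. Under Randomization and blinding it regards such discomfort as noticeable enough to let experienced patients guess their allocation.

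A significance test on 25 patients per arm is poorly suited to that question. It will often be non-significant when the thread does add harm, and a non-significant p-value does not tell the reader which excesses remain plausible. The pilot is meant to supply data for a full-scale trial, and that trial needs the size and uncertainty of the difference. For efficacy, the Clinical relevance section warns that statistical and clinical significance differ and adds responder thresholds. The adverse-event comparison has no counterpart.

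**Working it through.** **Inputs from the article**
- 20 patients per group and 20% drop-out (Sample size); equal allocation (Design).
- Safety analysed in all randomized patients, threshold 0.05 (Statistical analysis).
- Chi-square or Fisher's exact test for frequencies (Statistical analysis).

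**Assumptions, because the article is silent**
- The test is two-sided.
- Frequency means the number of patients with at least one event.
- Sham rates run from 0% to 70%, with a real-TEA rate 20 points higher.

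**Step 1. The article's own figure.** 20/(1 − 0.20) = 25 per arm, and 2 × 25 = 50. This reproduces the stated total. Safety uses all randomized patients, so 25 per arm is the relevant number.

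**Step 2. Probability of missing a 20-point excess.** With X ~ Bin(25, p₀ + 0.20) for real TEA and Y ~ Bin(25, p₀) for sham, power is the sum of P(X=x)·P(Y=y) over all tables (x, y) with p<0.05. The miss rate is 1 − power.

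| Sham vs real | Uncorrected chi-square misses | Fisher misses |
|---|---|---|
| 0% vs 20% | 23.4% | 61.7% |
| 2% vs 22% | 33.6% | 61.0% |
| 5% vs 25% | 44.5% | 63.0% |
| 10% vs 30% | 55.0% | 69.5% |
| 20% vs 40% | 64.8% | 76.9% |
| 30% vs 50% | 66.6% | 76.8% |
| 40% vs 60% | 66.4% | 76.3% |
| 70% vs 90% | 55.0% | 69.5% |

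The 50% and 60% sham rates give the same values as 30% and 20%, by symmetry. For sham rates of 10-70%, the miss rate is therefore about 55-67% with chi-square and 70-77% with Fisher. Power is about 23-45% across the two tests.

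**Step 3. Dependence on the choice of test.** Take 5/25 real against 0/25 sham.
- Fisher, two-sided: 2 × C(25,5)/C(50,5) = 2 × 53,130/2,118,760 = 0.0502, not significant.
- Uncorrected chi-square: 50 × (5×25 − 0×20)²/(25×25×5×45) = 5.56 on 1 df, p = 0.018, significant.
- Risk difference: +20 points, 95% Newcombe interval +3 to +39.

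The two permitted tests disagree, while the interval reports the same excess whichever is run.

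**Step 4. What a clearly non-significant result leaves open.** With 8/25 against 3/25, Fisher gives p = 0.17. The risk difference is 32% − 12% = +20 points, with a 95% Newcombe interval of −3 to +41. An excess of 40 points is still compatible with the data.

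**Step 5. Event types with no cases.** The exact one-sided 95% upper bound for 0/25 is 1 − 0.05^(1/25) = 0.113. Seeing none of an event in 25 treated patients still allows a rate of 11%.

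**The case against.** The strongest reply has four parts.

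- **A reader might infer that this test is the trial's only between-arm safety comparison.** It is not, because durations are compared too. That corrects the scope, and the point here is limited to frequency. The duration comparison does not fill the gap: it is another significance test, it covers only events that occurred, and it cannot show that more patients had events. For the same reason, no power figure based on 25 durations per arm applies.
- **A reader might infer that a null result will be reported as safety.** The article says no such thing. It calls the trial preliminary and lists the small sample as a limitation. This part of the reply stands: the misreading is a risk, not a plan.
- **The miss rates rest on assumed event rates.** They do. At sham rates of 0-5%, chi-square misses fewer than half of such excesses, so one headline range without its conditions would mislead. The 5/25 against 0/25 table lies on the threshold, and a common small-count convention would favour Fisher there, but the article states no rule for choosing.
- **Intervals are a detail for the analysis plan, and safety is secondary in a pilot.** Published counts and percentages would let a reader compute an interval. That lowers the severity. It does not remove the point, because the article goes beyond silence: it names a method, and that method does not fit its comparative safety aim.

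**Conclusion.** The concern holds for adverse-event frequency. The stated inference is a 0.05-level test with about 25 patients per arm. If frequency means patients with at least one event, and the test is two-sided, it misses a 20-point excess about 55-67% of the time (uncorrected chi-square) or 70-77% (Fisher) at sham rates of 10-70%. At sham rates of 0-5% the figures are about 23-44% and 61-63%. All these rates are assumptions.

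This is not an error that invalidates the trial, and the article does not equate non-significance with safety. It is a weak choice of method for a stated aim, with a better one available from the same data. It is worth changing as a low-cost improvement.

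**What to change.** In the safety part of Statistical analysis:

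1. Make the main adverse-event comparison the risk difference, real minus sham, in patients with at least one event, and likewise for each main event type, with a 95% Newcombe or exact interval.
2. For event types with no cases in an arm, give the exact one-sided 95% upper bound.
3. If the chi-square or Fisher p-value is kept, label it descriptive.
4. State that the comparative safety statement rests on the interval, in particular its upper limit, and that p≥0.05 will not be described as safe or as no different from sham.

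This takes a few sentences and a little extra output, with no added patients or data. The intervals will be wide: at 25 per arm the simple normal half-width, 1.96·√[p₀(1−p₀)/25 + p₁(1−p₁)/25], is about 19 points at 5% vs 25% and 27 points at 40% vs 60%. The safety statement will therefore be less favourable than a bare non-significant p-value would suggest.

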## Background

Non-specific chronic neck pain (CNP) is a common health problem, affecting 30–50% of the general population, and 23% of those individuals with CNP develop a recurrent episode within a month after their recovery [1, 2]. Of adult Europeans, 19% have chronic pain seriously affecting their daily activities and, of those, 20% have neck pain [3]. In the United Kingdom, 29% of adults experienced back or neck pain in the prior month, with half of those reporting chronic pain [4], and these observations are similar to those on a United States survey [5]. According to a survey conducted between 2007 and 2008 in Korea, the lifetime prevalence of neck pain is 20.8% [6]. CNP is also common in most occupational groups and is related to disability in both social and occupational groups because 11.0–14.1% of workers are limited in their activities each year [1, 7–9]. The economic burden associated with neck pain is increasing because many patients tend to continue to utilize health care resources for treatment for up to 10 years after the initial onset [10, 11].

Various non-surgical treatments, such as non-steroidal anti-inflammatory drugs (NSAIDs), muscle relaxants, analgesics, physiotherapy, interdisciplinary rehabilitation, education, and spinal injection, are available for the treatment of patients with CNP [12–14]. Although pain-relieving medication is most frequently used to alleviate CNP, long-term NSAID use is limited due to the risk of side effects and patient intolerance [15, 16]. On the other hand, acupuncture has been increasingly recognized as being clinically beneficial because it has been consistently reported to be effective and safe in reducing pain and improving quality of life for patients with neck pain [13, 17–19].

Thread-embedding acupuncture (TEA) is a special type of acupuncture designed to embed thread at targeted tissue by using a hollow needle. Absorbable suture materials, such as polydioxanone (PDO), catgut, PCL (polycaprolactone), etc., are used for the threads in the TEA devices [20]. PDO thread has been used in TEA devices in Korea while catgut thread is used in China. PDO thread is known to take approximately 180 days after implantation to be completely absorbed by the tissue [21]. TEA is considered to have longer therapeutic effects through continuous stimulation by the threads embedded at the acupoints.

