### Adverse events and safety

In this study, various post-intervention responses, such as pain, stiffness, and irritation, will be identified as adverse events related to the TEA treatment. Researchers will record the kinds of these adverse events, as well as the day that the adverse event occurs and is over. The duration of each adverse event will be recorded as a treatment outcome to compare between-group differences. Any causal relationship between the TEA treatment and adverse events will be evaluated using a 6-grade scale (1 = definitely related, 2 = probably related, 3 = possibly related, 4 = probably not related, 5 = definitely not related, and 6 = unknown), and the seriousness of the adverse events will be scored using a 4-point Spilker scale (1 = mild, 2 = moderate, 3 = severe, and 4 = extremely severe). If any serious adverse event (SAE) occurs, the researcher will immediately inform the SAE to the primary investigator (PI). The allocation status of the subject will be disclosed to the PI only, and the PI will report the SAE to the Ethics Committee so that a decision can be made regarding whether the subject needs to withdraw from the trial. All unexpected and unintended adverse events (AEs) will be recorded at each visit. During the screening and follow-up (week 6) periods, every participants will undergo blood tests, including liver function, blood glucose, and kidney function; every female participant will also receive urine pregnancy tests.

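### Adverse-event durations are compared event by event with independent-sample tests, although one participant can contribute several correlated events

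*Protocol article*

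**What the plan says.** Adverse events and safety sets out what is collected: "Researchers will record the kinds of these adverse events, as well as the day that the adverse event occurs and is over". It then gives duration the status of an outcome: "The duration of each adverse event will be recorded as a treatment outcome to compare between-group differences". Expected reactions after needling, namely pain, stiffness and irritation, are classed there as adverse events related to treatment.

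Statistical analysis names the test: "The duration of each adverse event will be compared between the two groups by using the Wilcoxon rank sum test", or the t test. For counts, it says that "all adverse events will be recorded as frequencies with percentages and durations", and that a chi-square or Fisher's exact test "will be used to evaluate the statistical significance of between-group differences in the frequencies of adverse events". The safety population is also stated: "Safety will be analyzed using the ITT set".

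Interventions fixes four weekly sessions for everyone, and the Abstract gives 14 acupoints per session. The article names no participant-level summary of duration and no method for several events in one person.

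**The concern.** An item with its own start day and end day is an occurrence. As worded, the observation in the duration test is therefore the single event, not the person. Someone who reacts strongly or recovers slowly after one session is likely to do so after the next, so durations from one participant are correlated. A two-sample rank sum or t test that pools them overstates the amount of information and rejects a true null too often.

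Reading the phrase as each type of event does not remove the problem. Stiffness, for example, can recur after each of four sessions, and no rule reduces the recurrences to one value per participant.

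A second, smaller point is that a duration exists only where an event occurred. The test therefore compares subsets formed after randomisation. If the thread changes who has a reaction, the two subsets are no longer comparable by design.

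Safety is in the trial's title, event duration is declared a between-group outcome, and the pilot is meant to inform a full-scale trial. A spurious difference in duration could be carried forward.

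**Working it through.** **The plan's own figure.** Sample size gives 20 per group with 20% drop-out. 20 / (1 − 0.20) = 25 per arm, 50 in total, which matches. The safety set is all randomised participants, so 25 per arm is used below. The article states no error rate for the safety comparison beyond the 0.05 level.

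**Inputs from the article.** Four sessions per participant; 25 per arm; significance level 0.05 (two-sided assumed); Wilcoxon rank sum or t test on durations.

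**Assumptions not in the article.** The probability of an event per session is 0.3 or 0.6, which gives on average 4 × 0.3 = 1.2 or 4 × 0.6 = 2.4 events per participant. Durations are log-normal. The within-person correlation (ICC) runs from 0 to 0.7 and applies to both occurrence (on a latent normal scale) and log duration. There is no true difference between arms, and each setting has 3,000 simulated trials.

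**Type I error when every event is an observation** (event probability 0.3 / 0.6):

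| ICC | Wilcoxon | t test |
|---|---|---|
| 0 | 0.049 / 0.055 | 0.044 / 0.049 |
| 0.1 | 0.052 / 0.065 | 0.048 / 0.056 |
| 0.3 | 0.089 / 0.118 | 0.071 / 0.106 |
| 0.5 | 0.144 / 0.178 | 0.124 / 0.141 |
| 0.7 | 0.204 / 0.233 | 0.181 / 0.213 |

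With one session only, so at most one event each (event probability 0.6), the Wilcoxon error is 0.048 at ICC 0.3 and 0.051 at ICC 0.5: no inflation.

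**Cross-check by formula.** Design effect DE = 1 + (m − 1) × ICC; true error = 2 × (1 − Φ(1.96 / √DE)).
- m = 4, ICC 0.1: DE = 1.3, error 0.086.
- m = 4, ICC 0.3: DE = 1.9, error 0.155.
- m = 4, ICC 0.5: DE = 2.5, error 0.215.
- m = 2, ICC 0.5: DE = 1.5, error 0.110.

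The formula with m = 4 gives every participant four events. The simulated values are lower because event counts vary, and they are the better guide.

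**With the participant as unit** (same simulations, four sessions):
- Wilcoxon on total duration, zero for event-free participants: 0.042–0.053.
- Wilcoxon on mean duration among participants with an event: 0.043–0.051. Restricting to those with events therefore does not inflate the error under the null; the difficulty is one of interpretation.
- Fisher's exact test on participants with at least one event: 0.000–0.037, conservative.

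**The case against.** The best reply is that the article never says events are treated as independent. Each adverse event could mean each type, with one value per participant, and a fuller protocol or analysis plan may say so. With one value per participant the error stays near 5%. That stands as a condition on the finding. It does not dispose of it, because the wording attaches start and end days to the item compared, and a type can recur over four sessions.

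It is also true that the size rests on assumed event rates and correlations, that the inflation is slight at a correlation of 0.1, and that this is a secondary outcome in a 50-person pilot with no stated decision resting on an adverse-event p-value.

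A reader might infer more than the article supports:
- *That the frequency test is invalid.* Percentages in a set of participants ordinarily count participants with an event, and Fisher or chi-square is then valid. Only a count of events would be a problem (0.116–0.161 in the same simulations at correlations of 0.3–0.5), and the article does not say that events are counted.
- *That unresolved events bias the result against or in favour of the thread.* The Background says "PDO thread is known to take approximately 180 days after implantation to be completely absorbed by the tissue", but that is absorption time, not the duration of a reaction. How open events are coded is a detail that an article may leave to the full protocol, and nothing says they are ignored.
- *That the as-allocated safety set gives a wrong answer.* Randomisation follows baseline assessment at visit 1, and a single unblinded practitioner uses devices that differ visibly. Nothing shows that untreated participants or device mix-ups would matter.
- *That the error is 16% or 22%.* Those values need four events from every participant.

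**Conclusion.** The point holds for the duration comparison, conditionally on the literal reading. If each event is pooled as an observation, a nominal 5% Wilcoxon test has a true error of about 5–7% at a within-person correlation of 0.1, 9–12% at 0.3 and 14–18% at 0.5, with up to four events per participant and 25 per arm. The t test is somewhat less affected. The direction is clear wherever participants have repeated, positively correlated events; the size depends on figures the article does not give, and it vanishes if nobody has more than one event. Comparing only those with events weakens the interpretation but leaves the null error rate intact. The article establishes no fault in the frequency test, in the handling of unresolved events or in the safety set. The consequence is limited to a secondary safety outcome, but the correction is cheap enough to be worth making.

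**What to change.** Change the wording in Statistical analysis as follows:

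- Compare total adverse-event days per participant up to week 8, with zero for those without events, by Wilcoxon rank sum, overall and by type of event. State how overlapping events are counted.
- State that the Fisher or chi-square test compares the number of participants with at least one event.
- Report per-event durations descriptively, without a test.

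A log-rank test on each participant's longest event would not serve, because it again uses only those who had an event.

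The cost is analysis wording only, since onset and end days are already recorded. The downside is that total days combine how often events occur with how long they last, which is why per-event durations should still be summarised alongside.
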